### Intervention strategies

The family members of the subjects will be informed about the purpose and methods of prone position ventilation, and their consent will be obtained for participation in the study.Careful assessment of the disease status will be performed and adequate fixation of the various cannulas and vascular catheters will be ensured.Enteral nutrition will be suspended 30 min before and the gastrointestinal nutrition tube will be closed before preparing for prone positioning.The timing of start of prone position ventilation will be determined by a team of medical personnel after determining the following: (1) the child has a stable circulation and shows no restlessness, and (2) the routine medical care has been provided.The child will be placed in the prone position with the participation of researchers, doctors, and the nursing staff. The child’s head will be tilted to one side to avoid damage to the eyes and nose due to compression; the arms will be bent upwards and placed on both sides of the head in a W-shaped configuration. The arms can also be placed in another position depending on the specific situation. Both lower limbs will be bent downwards to form an “M” shape; soft pillows will be used below both knee joints to avoid compression.Meticulous care will be exercised to ensure smooth fixation of mechanical ventilation, endotracheal tube, and various catheters.The depth of sedation will be calibrated during the entire prone position ventilation period to achieve good man-machine synchronization.Requirements during prone position ventilation: (1) adequate suction of the sputum and (2) the mechanical ventilation tube is suspended in the air, and the head is in left or right side position for 1–2 h.In a crossover design, the prone position will be maintained for 6–8 h per day until the improvement in oxygenation index (mean airway pressure × FIO_2_ × 100)/PaO_2_). Oxygenation index exceeding the baseline value or chest X-ray or CT findings suggest lung tissue recruitment. Prone position will be discontinued in case of deterioration of the condition (such as development of hemodynamic instability, pneumothorax, mediastinal emphysema, catheter loss, facial trauma, or formation of pressure ulcer).

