## Participants and recruitment

### Inclusion and exclusion criteria

A total of 68 infants who qualify the following criteria will be included in the study:
PALI after surgery for congenital heart disease or patients in whom chest X-ray and CT findings indicate PALI. The diagnostic criteria for PALI: (1) acute onset; (2) hypoxemia, oxygenation index ≥ 4; and (3) chest radiograph showing bilateral lung infiltratesInvasive mechanical ventilationAge range: 0–12 monthsPatients with stable hemodynamic status, more than 72 h after surgery. Hemodynamic stability defined as Inotropes stable (IS < 10) or based on ECHO (ejection fraction > 50%)Informed consent of family membersThis study has been approved by the Ethics Committee of the Children’s Hospital of Fudan University, No. (2020) 130

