## Outcomes

### Outcomes (effectiveness)

Main outcome indicators: lung compliance, SPO_2_, respiratory rate, peak, positive end-expiratory pressure (PEEP); laboratory indices: oxygenation index (mean airway pressure × FIO_2_ × 100)/PaO_2_), oxygen partial pressure (PaO_2_), carbon dioxide partial pressure (PaCO_2_), pH; chest radiograph.Secondary outcome indicators: (1) duration of mechanical ventilation; (2) length of stay in cardiac intensive care unit (CICU); (3) incidence of reintubation; (4) incidence of complications: pressure skin injury, slippage of the intubation, compression, and displacement of the pipeline; (5) hemodynamic stability: heart rate (HR), invasive arterial blood pressure (ABP), central venous pressure (CVP).

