### Sample size/power calculation

According to pre-experimental investigations, the average oxygenation index required by the experimental group of children is 276, with a standard deviation of 68, and the control group has an average oxygenation index of 228, with a standard deviation of 67. Comparing the two independent sample means, *α* = 0.05, *β* = 0.2, the Gpower sample calculation software showed an effect size of 0.71. The ratio of the test group and the control group is 1:1. An attrition rate of 10% has been factored in the sample size calculation. The calculated sample size is 34 patients per group and total sample size is 68 patients.

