## Trial status

The preliminary experiment is finished; follow-up is ongoing.

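### The oxygenation index worsens as it rises under the printed formula, but the recruitment sentence and the sample size treat a rise as benefit

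*Protocol article*

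**What the plan says.** Five places in the protocol article bear on the direction of the index.

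- *Inclusion and exclusion criteria*: PALI requires "hypoxemia, oxygenation index" of at least 4, so a high value is bad.
- *Intervention strategies*: proning continues 6–8 h per day "until the improvement in oxygenation index", with the formula in brackets. The next sentence reads "Oxygenation index exceeding the baseline value or chest X-ray or CT findings suggest lung tissue recruitment". The sentence after that begins "Prone position will be discontinued in case of deterioration of the condition" and gives examples.
- *Outcomes (effectiveness)*: the main outcome indicators include "oxygenation index (mean airway pressure × FIO_2_ × 100)/PaO_2". The Abstract names this index and lung compliance as the main outcome measures.
- *Sample size/power calculation*: "the average oxygenation index required by the experimental group of children is 276" (SD 68), and "the control group has an average oxygenation index of 228" (SD 67).
- *Trial status*: "The preliminary experiment is finished; follow-up is ongoing".

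**The concern.** PaO2 is in the denominator of the printed formula, so the index falls as oxygenation improves. The entry rule uses it that way. The recruitment sentence and the planning means use it the other way. This is more than one slipped word: the formula is printed twice and matches the entry rule, while the opposite direction also appears twice. Correcting the word in *Intervention strategies* alone would leave *Sample size/power calculation* in conflict with *Outcomes (effectiveness)*.

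Three things depend on the answer:

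- **Main outcome.** A reader cannot tell which index will be analysed, or which sign of the difference favours prone.
- **Sample size.** The 68 infants were sized on a quantity that appears not to be the printed outcome.
- **Treatment rule.** If the recruitment sentence is read as explaining when proning has succeeded, a worsening infant meets the index criterion for improvement. An improving infant does not meet it and stays prone unless imaging shows recruitment. This reading is an inference from where the sentence stands.

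**Working it through.** **Inputs from the protocol article.** Index = MAP × FiO2 × 100 / PaO2 (MAP is mean airway pressure); entry threshold 4; planning means 276 and 228, SDs 68 and 67; α 0.05, β 0.2; 10% attrition; 34 per group. MAP, FiO2 and PaO2 values below are assumptions, because the article gives none. PaO2 is taken in mmHg unless stated; the article gives no unit.

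**1. The plan's own figure.** Pooled SD = √((68² + 67²)/2) = 67.5. Effect size = (276 − 228)/67.5 = 48/67.5 = 0.711, matching the stated 0.71. A two-sided normal approximation gives 31.04 per arm, and 31.04/0.9 = 34.5, close to the stated 34. The calculation therefore belongs to the 276 and 228 scale.

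**2. Can 276 and 228 be the printed index?** Implied PaO2 = MAP × FiO2 × 100 / index.

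| MAP, FiO2 | PaO2 at 276 (mmHg) | PaO2 at 228 (mmHg) |
|---|---|---|
| 8, 0.4 | 320/276 = 1.2 | 320/228 = 1.4 |
| 12, 0.6 | 720/276 = 2.6 | 720/228 = 3.2 |
| 20, 1.0 | 2000/276 = 7.2 | 2000/228 = 8.8 |

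None is plausible. Conversely, at FiO2 1.0 and PaO2 40 mmHg the MAP needed is 228 × 40/100 = 91 cmH2O, or 276 × 40/100 = 110 cmH2O. If the values were nevertheless on this index, prone would be planned to do worse.

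**3. Do they fit PaO2/FiO2?** Both are ordinary values of that ratio, and prone is then better. The printed index follows as 100 × MAP / (PaO2/FiO2), at equal MAP in both arms.

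| MAP | Prone (276) | Control (228) | Prone minus control |
|---|---|---|---|
| 8 | 2.90 | 3.51 | −0.61 |
| 12 | 4.35 | 5.26 | −0.92 |
| 20 | 7.25 | 8.77 | −1.53 |

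These lie on the scale of the entry threshold of 4. Converting group means through a reciprocal is approximate, so the differences are illustrative and do not estimate the planned effect. Power on the printed index cannot be computed without an SD on that scale.

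**4. One infant who worsens.** PaO2 falls from 90 to 60 mmHg at unchanged settings.

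| MAP, FiO2 | Printed index | PaO2/FiO2 |
|---|---|---|
| 8, 0.4 | 3.6 to 5.3 | 225 to 150 |
| 12, 0.6 | 8 to 12 | 150 to 100 |
| 15, 0.8 | 13.3 to 20 | 112.5 to 75 |

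Each time the printed index exceeds its baseline, which the recruitment sentence reads as favourable.

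**The case against.** The strongest reply is that the operative instruction is to prone until the index improves, which is right for either index. The recruitment sentence does not say that proning stops there, and its wording could loosely mean better than baseline. Clinicians also see PaO2, FiO2 and SpO2, imaging is an alternative criterion, and the deterioration clause is open-ended. This stands as a limit on bedside harm, which is conditional and should not carry the point alone. It does not explain the planning means, and a rising index is not among the listed examples of deterioration.

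Second, the article gives no unit for PaO2. In kPa, the last row of step 2 becomes 7.2 and 8.8 kPa, about 54 and 66 mmHg, which are possible values. But MAP 20 with FiO2 1.0 is extreme as a group average. The entry threshold would no longer discriminate: at MAP 8 and FiO2 0.4, an index of 4 would correspond to 320/4 = 80 kPa, about 600 mmHg. Prone would still be planned to do worse.

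Third, PaO2/FiO2 is never named; it is inferred from scale and direction. That is true, and the conflict of direction does not depend on it.

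Fourth, the t tests in *Statistical analyses* give the same numbers whichever direction is favourable. That is correct, but it settles neither which index is tested nor which sign is benefit.

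Finally, an article condenses a fuller document. Here the issue is contradictory stated text, not an omission.

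**Conclusion.** The concern holds and must be corrected. The printed formula and the entry rule make a higher index worse; the recruitment sentence and the planning means make it better. Nothing in the article shows which is the mistake. With PaO2 in mmHg, the planning means cannot be values of the printed index at any realistic setting. Read as PaO2/FiO2, the planned +48 for prone becomes about −0.6 to −1.5 on the printed index, assuming equal MAP of 8 to 20. The mismatch between the sample-size index and the printed main outcome is the firmest consequence. The effect on the proning rule depends on how staff read the recruitment sentence, and the number of infants affected cannot be known from the article.

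**What to change.** Choose one index for the proning criterion, the outcome and the sample size, and state its direction of improvement wherever it is used. The clinical team should choose before seeing any results by group.

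- **Option A, keep the printed formula.** Reword the recruitment sentence so that an index below baseline suggests recruitment. Restate the planning means and SDs on that scale from the pre-experiment data, and recheck the sample size.
- **Option B, use PaO2/FiO2.** Name it for the proning criterion, the outcome and the sample size, and keep the recruitment sentence's direction. Label the entry threshold of 4 separately as the mean-airway-pressure index.

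Under either option, print the index and its direction on the bedside form. Because follow-up is ongoing, record which index and direction were applied to infants already treated. Keep mean airway pressure, FiO2 and PaO2 for every infant so that either index can be recomputed.

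The cost is corrected wording in the four sections concerned, a form update and a notice to staff. Option A adds the sample-size recheck. Option B redefines a printed main outcome during the trial, so it needs a documented amendment with its date and reason.

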## Outcomes

### Outcomes (effectiveness)

Main outcome indicators: lung compliance, SPO_2_, respiratory rate, peak, positive end-expiratory pressure (PEEP); laboratory indices: oxygenation index (mean airway pressure × FIO_2_ × 100)/PaO_2_), oxygen partial pressure (PaO_2_), carbon dioxide partial pressure (PaCO_2_), pH; chest radiograph.Secondary outcome indicators: (1) duration of mechanical ventilation; (2) length of stay in cardiac intensive care unit (CICU); (3) incidence of reintubation; (4) incidence of complications: pressure skin injury, slippage of the intubation, compression, and displacement of the pipeline; (5) hemodynamic stability: heart rate (HR), invasive arterial blood pressure (ABP), central venous pressure (CVP).

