**Methods:**

A single-center, randomized controlled trial of pediatric patients with acute lung injury after surgery for congenital heart disease who will receive prone position ventilation or usual care (control group). A total of 68 children will be enrolled according to the inclusion criteria. The main outcome measures will be lung compliance and oxygenation index. The secondary outcomes will be duration of mechanical ventilation, length of stay in cardiac intensive care unit, reintubation rate, and complication rate.

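### The abstract names two main outcomes and the Outcomes section names ten, while the sample size rests on one, and nothing says which result decides the trial

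*Protocol article*

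**What the plan says.** The abstract (Methods) states: "The main outcome measures will be lung compliance and oxygenation index".

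The section Outcomes (effectiveness) gives a longer list under the same label: "Main outcome indicators: lung compliance, SPO_2_, respiratory rate, peak, positive end-expiratory pressure (PEEP); laboratory indices: oxygenation index", followed, after the formula for the index, by "oxygen partial pressure (PaO_2_), carbon dioxide partial pressure (PaCO_2_), pH; chest radiograph". That makes ten: lung compliance, SpO2, respiratory rate, peak, PEEP, oxygenation index, PaO2, PaCO2, pH and chest radiograph. Secondary outcomes come afterwards under their own label, so all ten are presented as main.

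The sample-size section uses one variable: "the average oxygenation index required by the experimental group of children is 276, with a standard deviation of 68". For controls it takes a mean of 228 (SD 67) on the same index. The design values are "Comparing the two independent sample means, *α* = 0.05, *β* = 0.2", leading to 34 infants per group and 68 in total after a 10% attrition allowance.

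Statistical analyses assigns a test to each type of variable. It gives no significance level, no order among outcomes and no time point for the between-group comparison, though it mentions a paired comparison from before to after proning. Trial status reports that follow-up is in progress.

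**The concern.** A confirmatory trial needs one result, or one stated combination of results, that decides it. Here two sections of the same article give different sets of main outcomes, and the sample size supports only one member of either set. With no ranking, a reader of the results could not tell whether a finding on PaCO2, say, answers the trial's question or is one of several looks.

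Two things are at stake. One is the false-positive risk, which grows with the number of outcomes treated as main. The other is power: if the main outcomes were all kept and properly protected, 68 infants would be too few on the plan's own effect size. The lack of a common assessment time adds to the problem, because even the one comparison that was sized is not fixed in time for the control arm.

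**Working it through.** **Inputs.** Oxygenation index means 276 and 228, SDs 68 and 67, alpha 0.05, power 0.80, 1:1 allocation and 10% attrition (all Sample size/power calculation). Two main outcomes (abstract) or ten (Outcomes). Correlations between outcomes are not given, so 0 to 0.8 is assumed.

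**1. The plan's own figure.** Pooled SD = √((68² + 67²)/2) = 67.50. Effect size = (276 − 228)/67.50 = 0.711, matching the stated 0.71. The two-sided normal approximation, 2 × (1.960 + 0.842)²/0.711², gives 31.04 per arm. With attrition this is 31.04 × 1.1 = 34.1 or 31.04/0.9 = 34.5, so the stated 34 per group is reproduced to within rounding. (One-sided testing gives 28–29 and does not fit. An exact two-sided t-test calculation gives 33 evaluable and 37 with attrition; that is a separate matter.) The 68 is therefore the size for **one** comparison at the full 0.05.

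**2. False-positive risk if each main outcome is tested at 0.05.** For k independent outcomes it is 1 − 0.95^k. For correlated outcomes it was simulated with equally correlated normal test statistics (400,000 draws).

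| Assumed correlation | 2 outcomes | 10 outcomes |
|---|---|---|
| 0 | 9.75% | 40.1% |
| 0.3 | 9.5% | 35.1% |
| 0.5 | 9.1% | 28.6% |
| 0.8 | 7.9% | 17.3% |

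**3. What keeping several main outcomes would cost.** This uses Bonferroni and assumes an effect size of 0.711 for each outcome.

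| Main outcomes | Alpha each | Power, 34 per arm | Power, 30 evaluable per arm | Evaluable per arm for 80% | Total with 10% attrition |
|---|---|---|---|---|---|
| 1 | 0.05 | 82% | 77% | as stated | 68 (stated) |
| 2 | 0.025 | 74% | 67% | 39 | 2 × 44 = 88 |
| 10 | 0.005 | 51% | 44% | 55 | 2 × 62 = 124 |

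**4. Is the sized variable one of those listed?** By name, yes. By value, it does not fit. The Outcomes section defines the index as mean airway pressure × FIO2 × 100 / PaO2. As FIO2 cannot exceed 1, a value of 276 needs a mean airway pressure at least 2.76 times PaO2 numerically. The entry criterion is an index of 4 or more, and the planning means are 228/4 = 57 and 276/4 = 69 times that threshold. With PaO2 in the denominator, better oxygenation also lowers the index, yet the planned experimental mean is the higher one. The definition has to be reconciled before this measure can serve as the primary outcome.

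**The case against.** The strongest reply is that this is a condensed article. A multiplicity rule and a measurement schedule commonly sit in the analysis plan or full protocol, neither of which is shown. That stands for the rule and the schedule as such. It does not cover the conflict: the article prints both lists and they differ, and an analysis plan takes its primary outcome from the protocol.

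Several stronger readings are tempting but not supported:

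- **Every outcome is tested at 0.05 and any one can carry the trial.** The 0.05 appears only in the sample-size section, and no rule for declaring success is stated. The error rates above are conditional on that assumption.
- **The false-positive risk is 40%.** That is the ceiling for ten independent outcomes. PaO2 is part of the oxygenation index, SpO2 tracks PaO2, and pH tracks PaCO2, so the range of 17–40% is fairer.
- **Outcomes are assessed at an outcome-dependent moment.** Under Intervention strategies, improvement in the index governs how long daily prone sessions continue. It is not given as an assessment time, and the analysis section has a separate before-and-after comparison. The text supports only that no time common to both arms is stated.
- **PEEP, respiratory rate and peak merely reflect choices of the unblinded team that turns the infant.** The article says "The child will be placed in the prone position with the participation of researchers, doctors, and the nursing staff". It does not say who sets the ventilator, or whether rate and peak are set or measured values. The argument would also touch the oxygenation index, which contains mean airway pressure and FIO2.

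**Conclusion.** The point holds as a stated contradiction: two main outcomes in one place, ten in another, a sample size for one, and no ranking. Followed as written, the plan yields no single deciding result.

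Its size depends on assumptions. With each main outcome tested at 0.05, the chance of at least one false positive is about 8–10% for two outcomes and 17–40% for ten, for correlations from 0.8 down to 0. Even the lowest figure for ten is more than three times 5%. The power and sample-size costs further assume an effect size of 0.711 for every outcome. This needs correcting before any between-arm result is seen, because afterwards the choice of primary outcome could not be shown to be independent of the data.

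**What to change.** 1. Name the oxygenation measure used for the sample size as the sole primary outcome. First reconcile its definition, so that the formula, the entry threshold and the planning means of 276 and 228 describe the same quantity.
2. Assess it at one pre-specified time after randomisation, the same in both arms, chosen from the existing measurement schedule.
3. Make lung compliance the first secondary outcome, tested only if the primary is significant. Move the other eight to secondary or descriptive status.
4. Align the abstract and the Outcomes section.
5. Because follow-up is ongoing, make the change without sight of between-arm outcome data, and date and disclose it in the registry.

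The cost is wording, a documented amendment and fewer outcomes that can carry a confirmatory claim. The stated 68 is unchanged, provided the planning means and SDs describe the reconciled measure at the chosen time; the article does not say when those values were taken. Since no measurement schedule is shown, it cannot be confirmed from the article that a suitable common time already exists. Keeping the abstract's pair as co-primary outcomes with split alpha is a legitimate alternative, but would need about 88 infants on the assumptions above.

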**Table Taba:** 

Inclusion criteria	Exclusion criteria
**- Pediatric patients with lung injury after** surgery for **congenital heart disease or** those in whom **chest X-ray** and **CT** findings indicate the need for augmenting pulmonary drainage due to **pulmonary complications**.	-Hemodynamic instability, severe hypotension, ventricular arrhythmia - Pacemaker dependent - ECMO
**- Invasive mechanical ventilation**	-Intracranial hypertension
**-**Age range: **0–12 months**	-Active acute bleeding
**-Stable hemodynamics, more than 72 h after surgery**	-Spinal injuries and untreated unstable fractures, orthopedic surgery or recent abdominal surgery
**-Informed consent of family members**	-Facial trauma
	Severe pneumothorax
	-Patients with delayed chest closure and wound infection requiring immobilization

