### Statistical analyses

The SPSS 23.0 statistical software will be used for statistical analyses. Quantitative variables conforming to normal distribution will be presented as mean ± standard deviation. Between-group differences will be assessed using the *t* test (paired *t* test before and after prone position, hemodynamic indicators, oxygenation indices, etc., will be assessed using group *t* test). Non-normally distributed quantitative variables will be presented as Chinese numbers (quartiles), and non-parametric tests will be used to assess between-group differences. Categorical variables will be presented as frequency and percentage, and between-group differences will be assessed using chi-squared test or Fisher exact test.

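### Lung compliance, a main outcome, has no stated body-weight basis in infants aged 0–12 months and is compared by an unadjusted test, which can cost substantial power if raw values are used

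*Protocol article*

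**What the plan says.** The abstract of the protocol article states: "The main outcome measures will be lung compliance and oxygenation index". The section on effectiveness outcomes again puts compliance first ("Main outcome indicators: lung compliance"), followed by saturation, ventilator settings, blood gas values and the chest radiograph. Compliance appears there by name only. No unit is given, nothing says whether it is static or dynamic, and there is no per-kg or other size basis. The same section does print the formula for the oxygenation index.

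The eligibility table sets "Age range: 0–12 months". No weight limit or weight distribution is given. The block randomization section uses blocks of 4 and mentions no stratification by age or weight.

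The statistical analyses section gives the tests as "paired *t* test before and after prone position, hemodynamic indicators, oxygenation indices, etc., will be assessed using group *t* test". For non-normal variables, "non-parametric tests will be used to assess between-group differences". Compliance is not named in that section, and no weight or baseline covariate appears.

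**The concern.** A larger lung takes in more volume for the same pressure, so raw compliance differs between a newborn and a one-year-old even when their lungs are equally stiff. A test that compares raw values between arms carries this size variation in its error term. Compliance is one of the two outcomes on which the abstract rests the trial. If much of its spread is body size, a real effect of prone positioning could be missed, and a null result would be hard to interpret. Leaving the scale open also allows the choice between raw and per-kg values to be made after the data have been seen.

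**Working it through.** **The plan's own figure.** The sample size section works from the oxygenation index: means 276 and 228, SDs 68 and 67. The effect size is 48 / √((68² + 67²)/2) = 48 / 67.5 = 0.71, as stated. The normal approximation for a two-sided 5% test at 80% power gives about 31 per group. Allowing for 10% attrition, 31/0.9 = 34.4, in line with the stated 34. An exact t-test calculation would ask for 33 before attrition. None of this concerns compliance, for which no power calculation is stated.

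**Inputs for compliance.**
- From the documents: 34 per arm with 10% attrition built in, hence also 31 evaluable per arm; α = 0.05, taken as two-sided because the article does not say.
- Assumed, because the documents give no figures: a 20% relative difference between arms; a coefficient of variation (CV) of per-kg compliance, CVc, of 25–35%; a CV of body weight, CVw, of 25–45%; weight independent of per-kg compliance.

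**Formulas.** Raw compliance = per-kg compliance × weight. Under independence,

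CV(raw) = √((1 + CVc²)(1 + CVw²) − 1).

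The standardised effect is 0.20/CVc on the per-kg scale and 0.20/CV(raw) on the raw scale. Power is that of the two-sample t test.

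**Mid-range case**, CVc 0.30 and CVw 0.35: CV(raw) = √(1.09 × 1.1225 − 1) = 0.473. The variance ratio is (0.473/0.30)² = 2.48. The standardised effect falls from 0.667 to 0.423. Power with 34 per arm falls from 0.77 to 0.40.

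**Grid.**

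| CVc | CVw | CV(raw) | Variance ratio | Power per kg / raw, n = 34 | Power per kg / raw, n = 31 |
|---|---|---|---|---|---|
| 0.25 | 0.25 | 0.359 | 2.06 | 0.90 / 0.62 | 0.87 / 0.58 |
| 0.25 | 0.45 | 0.527 | 4.44 | 0.90 / 0.34 | 0.87 / 0.31 |
| 0.30 | 0.35 | 0.473 | 2.48 | 0.77 / 0.40 | 0.73 / 0.37 |
| 0.35 | 0.25 | 0.439 | 1.57 | 0.64 / 0.46 | 0.60 / 0.42 |
| 0.35 | 0.45 | 0.591 | 2.86 | 0.64 / 0.28 | 0.60 / 0.26 |

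The share of raw variance that comes from weight is 1 − 1/ratio: 36% at ratio 1.57, 60% at 2.48 and 77% at 4.44. With a weight CV of only 0.15, below the grid, and CVc 0.30, power at 34 per arm still falls from 0.77 to 0.67.

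**A second effect assumption.** Suppose the standardised effect of 0.71 applied to per-kg compliance. With 31 evaluable per arm, power is about 79% per kg. On the raw scale it runs from 72% (CVc 0.40, CVw 0.15) down to 23% (CVc 0.20, CVw 0.40). The direction is the same and the range is wide.

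**Type I error.** In simulation with no treatment effect, 31 per arm, CVc 0.30 and CVw 0.30 or 0.40, the raw-scale t test rejected in 4.9% and 4.7% of runs. The test stays valid.

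**The case against.** The strongest reply is that the article is silent on the unit and has not chosen raw values. A journal article condenses the full protocol, and a per-kg definition could stand there or in the analysis plan. A group t test works equally well on per-kg values. This stands: a reader might infer that compliance will definitely be analysed unscaled, and the documents do not support that. What the article does fix is the between-arm test, which is unadjusted. It also found room to define the oxygenation index in full but not compliance.

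A reader might also infer that body size will swamp the treatment effect, or that it makes up most of the variance. Neither is established. All the CVs are assumed, and at the low end of the grid weight accounts for 36% of raw variance.

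Nor is there bias. Randomisation balances weight in expectation. A chance imbalance between arms is already part of the raw-scale standard error and is not a second harm on top of the power loss.

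Finally, the article also plans a paired t test, which compares each child with itself and largely removes body size. That test is tied to before and after prone positioning, so it does not estimate prone against control. That contrast is left to the group test. It is also fair to say that the article claims no power for compliance, so no stated figure is contradicted.

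**Conclusion.** The point holds in conditional form. A main outcome that depends on body size is given with no size basis, in infants aged 0–12 months, and is paired with an unadjusted between-arm test. If raw values are used, the consequence is lost precision. Under the assumptions above, power for a 20% difference with 34 per arm is 0.28–0.62 raw against 0.64–0.90 per kg; with 31 evaluable it is 0.26–0.58 against 0.60–0.87. Power fell in every scenario examined, but the documents do not allow the size of the loss to be fixed. It should be corrected because it affects a headline outcome and the remedy is cheap. It does not threaten the validity of the comparison.

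**What to change.** In the outcome section, define the outcome as lung compliance per kg of body weight at randomisation (mL/cmH2O/kg), measured by the same method and at the same time point in both arms. In the statistical analyses section, replace the group t test for this outcome with an ANCOVA that compares the arms and adjusts for the pre-randomisation per-kg compliance. If the full protocol or analysis plan already defines compliance per kg, say so in the article; the change of test is still worth making.

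The cost is a line or two of text. Weight and ventilator compliance should already be in the routine chart, and the sample size need not change. The one practical demand is a compliance reading before randomisation in every infant.
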